### Endpoint criteria

Patients finish their training when either of the criteria is met:▪ Patients finish 3-year cognitive training;▪ Patients meet the diagnostic criteria of dementia due to AD, according to the National Institute on Aging-Alzheimer’s Association (NIA-AA) workgroups [7].

### Recruitment, screening and run-in period

Patients will be recruited from the memory clinic of 7 centers above. During the first week, each patient will perform MMSE and HAMD as screen. Then eligible patients will enter a run-in period of 2 weeks, during which they will receive blood tests, electrocardiogram, cranial MRI and a basic computer operation test. The blood tests contain complete blood count, liver and kidney function test, syphilis, folic acid level, vitamin B12 level, thyroid function and ApoE genotype. The purpose of the run-in period is to collect basic clinical data, rule out other causes of cognitive decline and evaluate participants’ compliance. Then all the eligible patients will be registered before baseline assessment.

### Baseline assessment and randomization

Baseline demographics include sex, age, education level, occupation, concomitant disease and medications. Physical exercise and diet style will also be recorded.

A neuropsychological battery for multiple cognitive domains will be performed by neuropsychological assessors who are blind to the following grouping. These tests included MMSE, the Chinese version of Alzheimer’s Disease Assessment Scale-Cognitive subscale(ADAS-Cog) [21], Alzheimer’s Disease Cooperative Study-Activities of Daily Living (ADCS-ADL) [21], the Auditory Verbal Learning Test (AVLT)-Huashan version [22], the Shape Trail Test (STT, including Part A and B) [23], the Rey-Osterrieth Complex Figure Test (CFT) [24], the Stroop Color-World Test (SCWT) and Boston Naming Test (see Additional file 1).

After the baseline assessment, patients will be randomly allocated into two groups, which will be managed by Ruijin Hospital with interactive web response system. The stratification factors will be balanced between two groups when allocation, including education level (university or not) and age (older than 65 years or not). Assessors will be specific in each center and blinded to the grouping.

### Ethics and informed consent

Conformed to the ethical principles proclaimed in the Declaration of Helsinki in 1964, and revised in Tokyo in 2004, the study protocol has been reviewed and thus approved by independent ethics committees in the Ruijin Hospital, which is the leading center of the study. Before the inclusion, written informed consent forms will be signed by patients or their surrogate family member after a detailed explanation. The SIMPLE study is registered with Chinese Trial Registry.gov and ClinicalTrial.gov (Register number: ChiCTR-INR-16008959 and NCT03119051).

### Intervention and follow-up

All the participants in the intervention group will login an online training website with their own passwords by either cell phone or tablet computer. A variety of cognitive domains will be involved in the training including memory, calculation, attention, visualspatial and executive skills. The difficulty level of each game will be adjusted automatically according to patients’ last training results so that patients’ accuracy rate will be kept between 70 and 80%. Patients will be required to play 3–4 times of 30 min’ training game every week. Training time and results will be uploaded immediately to a web server which could be monitored by investigators. In contrast, participants in the control group will be required to neither alter their daily lifestyle nor receive any additional cognitive training.

Investigators will conduct telephone follow-ups for both groups every two weeks to obtain their feedback and offer encouragement. On the other hand, follow-up assessment will be performed every six months (in month 6, 12, 18, 24, 30, 36 ± 2 weeks). In month 6, 18, 30, brief assessment including MMSE, ADAS-Cog and ADL would be done, while in month 12, 24 and 36, the neuropsychological battery at baseline for multiple cognitive domains will be performed. MRI is given in month 12 and 36 (Fig. 1).

**Fig. 1 Fig1:**
[figure not shown]
The SIMPLE study flowchart. The flowchart included the general protocol of recruitment, grouping, follow-up and final analysis

### Outcome measures

The primary outcome is the incidence of AD during the follow-up. The diagnosis of AD will be made according to NIA-AA criteria. The performance in each cognitive domain will be compared as secondary outcomes. ADAS-Cog will be used to assess the global cognitive performance of MCI patients. Memory will be assessed using the AVLT-H. Attention and executive functions will be evaluated by TMT and the Stroop task. Language will be assessed by Boston naming test (30-item version). Visual spatial ability and visual memory will be evaluated by the Rey–Osterrieth complex figure test (CFT). Activities of daily living will be assessed by ADCS-ADL. Structural and functional MRI will help to uncover the potential neural activity changes during training. The schedule of all the outcome measures is shown in the Table 2.

**Table 2 Tab2:** Outline and timelines of the trial

	Screening	Run-in	Baseline	1st Visits	2nd Visit	3rd Visit	4th Visit	5th Visit	Endpoint^a^
Time Points	−3 weeks	−2 weeks	0	6 months	2 months	18 months	24 months	30 months	36 months
Written informed consent		×							
Inclusion/exclusion criteria	×	×	×						
Blood test		×							
Electrocardiogram		×							
Cranial MRI examination		×			×				×
MMSE	×		×	×	×	×	×	×	×
ADAS-Cog			×	×	×	×	×	×	×
ADCS-ADL			×	×	×	×	×	×	×
HAMD/GDS	×		×		×		×		×
AVLT			×		×		×		×
TMT			×		×		×		×
CFT			×		×		×		×
Stroop Test			×		×		×		×
Boston Naming Test			×		×		×		×

^a^Endpoint is either the ending of 36-month follow-up or the diagnosis of AD during follow-up

### Neuroimaging markers

Structural and functional brain MRI will be performed at baseline, one-year follow-up and endpoint (Table 2). The MRI protocol is described in the Table 3. In structural MRI analysis, medial temporal lobe atrophy visual rating scale is used to indicate the level of atrophy in the medial temporal lobes (ranging from 0 to 3) [25]. According to cognitive ability changes, we also use voxel based morphometry (VBM) to quantitatively compare the volume of specific areas in brain. With regard to functional MRI, we use blood oxygen level dependent (BOLD) signal to find out functional changes related with cognitive performance changes. Fractional amplitude of low frequency fluctuation (fALFF), regional homogeneity (Reho) will be used to represent regional neural activities, while neural network changes are indicated by functional connectivity [26, 27].

**Table 3 Tab3:** Brain MRI protocol

Sequence name/Acquisition method	Field of View (mm)	Matrix	Slices	Inter-slice gap (mm)	Thickness (mm)	Voxel (mm^3^)	TR /TE (ms)
3D FSPGR	256 × 256	256 × 256	192	0	1	1 × 1 × 1	5.52/1.72
BOLD	240 × 240	64 × 64	33	0.7	3.5	3.5 × 3.5 × (3.5 + 0.7)	2000/30

*Abbreviations: TR* repetition time, *TE* echo time, 3D FSPGR three-dimensional fast spoiled gadient-recalled

### Sample size and statistical analysis

Sample size was estimated based on conversion rate from MCI to AD in the SAS study [28]. In the SAS sample, it was 6.0 per 100 person-years. In the three-year follow-up, the overall probability of conversion event would be 17%. We use hazard ratio (HR) to represent the converting difference of the training group per unit time as the control group. HR represents instantaneous risk over the all period, and is clinically significant due to its indication risks that happen before the endpoint. A power calculation was performed with the online freeware program by “time-to-event” method [29] (http://powerandsamplesize.com).

Due to HR as an almost unprecedented outcome in such sort of trial, we cautiously set 50% reduction in the rate of conversion as estimated effect. With 80–90% statistical power and 12% as the overall probability of conversion within the study period, 544–728 patients in total are considered the minimal number necessary to estimate the hazard ratio. Considering 10% dropout, we plan to enroll approximately 600–800 patients, with 300–400 patients in each group.

As an exploring study, we used per-protocol set instead of intention-to-treat (ITT) analysis as primary endpoint analysis in order to strictly estimate the effect of training. If participants were indicated cholinesterase inhibitors or memantine, or they could not insist on training, they would be excluded from per-protocol sets. ITT approach will also be done to avoid the effects of crossover and dropout. The results of these two analysis will be carefully interpreted.

The randomization is stratified by age and education years according to the Ruijin center using SAS statistical software (SAS Institute Inc., Cary, NC, USA) by a statistician ([name]) with no access to information on the patients or physicians. Patients will be randomized in a ratio of 1:1 to receive the training or only follow-up. In the randomization process, the randomized code is generated and assigned to physicians in a sealed envelope by the statistician. Afterwards, the sealed randomization codes are sent out to each center. The odd number means the training group, while the even number means the control group. If the patient cannot be trained because of difficulty in operating computer or cellphone, the patient will be managed as off-trial.

Continuous variables (scores of each cognitive assessment) will undergo mixed model analysis in the two groups for the secondary outcomes. At the same time, the effect of ApoE genotype on primary outcome will be observed through analysis of subgroups divided by ApoE genotype in both groups. With regard to MRI, VBM measures and BOLD signal will be used to find out structural and functional changes related with cognitive performance changes.

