### Study design

SIMPLE is a 3-year multicenter prospective single-blind clinical cohort study with two parallel arms in 1:1 ratio. Patients are randomized into the training group the control group (absence of training). The total training dose will be around 200 h, with 3–4 sessions per week and 30 min per session. Though dose effect was not well studied, we will give the training dose that is acceptable by MCI patients according to previous studies and our preliminary data. Global cognitive function and daily living activity will be assessed at baseline and every 6 months afterwards (in month 6, 12, 18, 24, 30 and 36), while specific cognitive domains (memory, executive function, attention and language) will be evaluated at baseline and every 12 months afterwards (in month 12, 24 and 36). In addition, brain structure and function will be assessed by MRI at baseline and in month 12 and 36. During the follow-up period, medications for dementia (ChEIs or memantine) are not indicated. If a patients converts to AD during follow-up, pharmacological therapy starts. Cognitive assessments for all cognitive domains and MRI will be performed at that time. Meanwhile, telephone follow-ups will be conducted every two weeks in both groups. As an single-blind trial, neuropsychological assessor will be blinded to the group allocation. The total duration of the study will be approximately 5 years, from June 2017 (first in) until June 2022 (last out).

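### As worded, the drug exclusion would take converters out of the primary per-protocol set, and the stated 80–90% power is not shown to apply to that set

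*Protocol article*

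**What the plan says.** All but one of these statements are in the protocol article, Sample size and statistical analysis.

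- **Effect and power.** The assumed effect is a halving of the conversion rate: "we cautiously set 50% reduction in the rate of conversion as estimated effect". The power inputs are "With 80–90% statistical power and 12% as the overall probability of conversion within the study period", and the result is "544–728 patients in total are considered the minimal number necessary to estimate the hazard ratio".
- **Allowance.** One inflation follows: "Considering 10% dropout, we plan to enroll approximately 600–800 patients, with 300–400 patients in each group".
- **Primary set.** For the primary endpoint, "we used per-protocol set instead of intention-to-treat (ITT) analysis as primary endpoint analysis". An ITT analysis is also planned.
- **Exclusions from that set.** "If participants were indicated cholinesterase inhibitors or memantine, or they could not insist on training, they would be excluded from per-protocol sets". No rate is given for either reason, and no point in follow-up is named after which the drug criterion stops applying.
- **Treatment at conversion.** The Study design section states: "If a patients converts to AD during follow-up, pharmacological therapy starts". Just before this it says that dementia drugs are not indicated during follow-up.

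Under Outcome measures, the primary outcome is the incidence of AD during follow-up.

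**The concern.** There are two separate problems, and the first is the more important.

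**Events.** Conversion to AD is the primary endpoint. It is also the only route the article describes by which a participant comes to need a dementia drug, since Table 1 forbids both drug classes during the trial. An exclusion triggered by the indication for such a drug, with no time limit, therefore selects on the outcome. Applied literally, it removes the events on which the hazard ratio and its power depend. Applied unevenly across centres, it would make the primary result depend on who was put on drug after diagnosis.

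**Power.** The 80–90% is calculated for all patients who do not drop out. The set declared primary is smaller if patients who stop training are removed as well. Controls receive no training, so this exclusion can reduce only the training arm. The schedule is 3–4 sessions a week for three years, so some exclusions are foreseeable. A null result on the primary set would then be read against a power worked out for a different set.

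**Working it through.** **1. The two sections side by side.**

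| Step | Section | Consequence |
|---|---|---|
| Patient is diagnosed with AD | Outcome measures | A primary event occurs |
| Drug therapy starts at conversion | Study design | The patient now has an indication for dementia medication |
| Anyone indicated a cholinesterase inhibitor or memantine is excluded | Sample size and statistical analysis | The patient leaves the per-protocol set |

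Nothing in the third step is limited to the time before the first. The Table 2 footnote makes the AD diagnosis an endpoint of follow-up, but the exclusion sentence does not refer to it.

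**2. Reproducing the plan's sample size.** Inputs from the article are a hazard ratio (HR) of 0.5, 1:1 allocation, 12% overall event probability and power of 80% and 90%. The significance level is not stated. Two-sided 5% is assumed, because with the Schoenfeld formula it reproduces the plan's figures.

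Events D = (z0.975 + z_power)² / (0.25 × (ln 0.5)²), and N = D / 0.12.

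- 80%: (1.960 + 0.842)² / (0.25 × 0.4805) = 65.3 events; N = 544.5.
- 90%: (1.960 + 1.282)² / (0.25 × 0.4805) = 87.5 events; N = 729.0.

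These match 544 and 728.

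**3. Power of a per-protocol set that loses part of the training arm.**

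Power = Φ(√(d·f·(1−f)) × |ln 0.5| − 1.960), where d is the number of events and f is the training arm's share of the set.

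Dropout is 10% in both arms, leaving 270 per arm from 600 and 360 per arm from 800. A further share x is then removed from the training arm only. The article gives no value for x, so 10%, 20% and 30% are assumptions.

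With HR 0.5 the two arms cannot both have 12% risk. If control survival is S, the training risk is 1 − √S. Solving ((1 − S) + (1 − √S)) / 2 = 0.12 gives 15.8% (control) and 8.2% (training).

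Worked case, 600 enrolled and x = 20%:

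- Controls 270; training 270 × 0.8 = 216.
- d = 270 × 0.1577 + 216 × 0.0823 = 42.6 + 17.8 = 60.4.
- f = 216 / 486 = 0.444.
- √(60.4 × 0.444 × 0.556) × 0.693 = 2.676; 2.676 − 1.960 = 0.716; Φ(0.716) = 76.3%.

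The same section gives a 17% three-year probability from its source cohort. Taking that as the control risk, the training risk is 1 − √0.83 = 8.9%.

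| Further training-arm exclusion (assumed) | 600, average 12% | 800, average 12% | 600, control 17% | 800, control 17% |
|---|---|---|---|---|
| 0% | 79.7% | 89.6% | 82.6% | 91.7% |
| 10% | 78.2% | 88.5% | 81.2% | 90.7% |
| 20% | 76.3% | 87.1% | 79.4% | 89.4% |
| 30% | 73.9% | 85.2% | 77.1% | 87.7% |

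**The case against.** **On the drug exclusion.** The intended target is probably drug use before the endpoint. The Study design section says dementia drugs are not indicated during follow-up and brings them in only at conversion, and Table 2 treats diagnosis as the endpoint. An exclusion that emptied the primary set of events would defeat its purpose. This is a fair account of intent, and a reader should not infer that the trial will in fact analyse a set without events. But no sentence limits the exclusion in time, and its literal wording says the opposite of what was probably meant.

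**On power.** The 10% may already contain some patients who stop training. Poor compliance is a withdrawal criterion, patients who cannot operate the device are managed as off-trial, and the run-in tests computer operation and compliance. The 12% is also lower than other rates in the article. With a 17% control risk, a further 10% exclusion still leaves 81.2% and 90.7%. The Background cites 25–30% three-year conversion. At 25% control risk even a 20% exclusion leaves about 92% at 600 and 97% at 800. All of this stands. It makes the loss conditional, but it does not link the 10% to the exclusions of the primary set.

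**On condensation.** A journal article may leave the power of each analysis set to a fuller document. That would excuse leaving out a second calculation. It does not settle which set the printed 80–90% describes.

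**A stronger reading to avoid.** Since 600 × 0.9 = 540 and 800 × 0.9 = 720 lie below 544 and 728, a reader might infer that enrolment fails even on dropout. It does not in any meaningful sense. The target is given as approximate, and power at 10% loss is 79.7% and 89.6%. That is rounding, not an error.

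**Conclusion.** The point holds in two parts.

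First, the drug exclusion and the start of therapy at conversion contradict each other as written. Taken literally, they remove primary-endpoint events from the primary analysis. This part needs no assumption beyond the text, and the passages must be reconciled.

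Secondly, the stated 80–90% power is not shown to apply to the per-protocol set. On the plan's 12%, a further 10–30% exclusion from the training arm costs about 1.5 to 6 points at 600 enrolled (79.7% down to 78.2–73.9%) and about 1 to 4.5 points at 800 (89.6% down to 88.5–85.2%). With a 17% control risk, power first falls below 80% and 90% at a 20% exclusion (79.4% and 89.4%).

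A reader might infer that the primary analysis definitely lacks the stated power. The article does not support that. It gives no exclusion rate, it leaves open whether the 10% covers some non-trainers, and at 800 enrolled power stays above 80% throughout the range shown. The figures also assume two-sided 5%, and that HR 0.5 and the arm risks carry over unchanged to the per-protocol set.

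**What to change.** 1. In the analysis-set definition, limit the drug exclusion to use of a cholinesterase inhibitor or memantine before the AD diagnosis. State that treatment begun because of conversion never removes an event. This defines who is analysed and changes nothing in how patients are treated.
2. Say whether the 10% covers patients who could not keep up training. Restate the power for the per-protocol set under an explicit assumed share of training-arm exclusions.

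The cost is a few sentences in Sample size and statistical analysis. No extra patients are needed. The stated power may become slightly less favourable, depending on the share assumed.

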Pharmacological and non-pharmacological treatments have been greatly concerned about their effects. Donepezil, rivastigmine, galantamine, and memantine are the drugs presently approved by the Food and Drug Administration (FDA) for treatment of AD. However, both cholinesterase inhibitors (ChEIs) and antiglutamatergic treatments are not indicated for MCI patients. A review and meta-analysis concluded that treatment with ChEIs merely affected MCI progression to dementia or improved cognitive test scores [9]. In one study of data from Alzheimer’s Disease Neuroimaging Initiative, MCI patients who received ChEIs with or without memantine were more impaired, showed greater decline in scores, and progressed to dementia sooner than patients who did not receive ChEIs [10].

In addition, as cognitive symptoms of MCI patients are still mild, drug compliance could be another problem. Moreover, costs and side effects of drugs are important negative factors of early medical treatment.

In recent years, cognitive training has gradually become an important therapeutic approach due to its convenience and effectiveness. It describes a group of brain games exercising mental processing ability such as attention, memory, calculation and so on [11]. An increasing number of studies have proved that cognitive training has beneficial effects on delaying cognitive decline in the elderly. The Advanced Cognitive Training for Independent and Vital Elderly (ACTIVE) study which did a 5-year follow-up of 2802 healthy aging people found that there was a significantly smaller proportion of cognitive decline and higher score of living abilities in the intervention group receiving various cognitive training [12]. Similar effects of cognitive training are also found in MCI patients. Sylvie Belleville et al. [13] found that both MCI patients and healthy elders who received an 8-week intervention focusing on teaching episodic memory strategies had better performance in episodic memory assessment than the control group. An randomized clinical trial of 100 MCI patients found that 6-month cognitive training improved significantly cognitive functions of the intervention group in multiple domains and this improvement was well maintained during a 18-month follow-up [14].

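### The per-protocol drug exclusion has no time limit, so read literally a patient can leave the primary analysis set because the primary endpoint was reached

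*Protocol article*

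**What the plan says.** All references are to the protocol article.

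- **Endpoint.** Outcome measures: "The primary outcome is the incidence of AD during the follow-up".
- **Primary analysis set.** Sample size and statistical analysis: "we used per-protocol set instead of intention-to-treat (ITT) analysis as primary endpoint analysis".
- **Drug exclusion.** Same section: "If participants were indicated cholinesterase inhibitors or memantine, or they could not insist on training, they would be excluded from per-protocol sets". No time window is given, and no exception for patients who have converted.
- **Drug therapy in follow-up.** Study design first says "During the follow-up period, medications for dementia (ChEIs or memantine) are not indicated", and in the next sentence "If a patients converts to AD during follow-up, pharmacological therapy starts".
- **Which drugs.** Background: "Donepezil, rivastigmine, galantamine, and memantine are the drugs presently approved by the Food and Drug Administration (FDA) for treatment of AD". These are three cholinesterase inhibitors and memantine, the two classes in the exclusion rule.
- **End of observation.** Table 2 footnote, under Outcome measures: "Endpoint is either the ending of 36-month follow-up or the diagnosis of AD during follow-up".

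An ITT analysis is also planned, and the article says that both sets of results will be interpreted with care.

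**The concern.** A per-protocol exclusion should depend on departures from the protocol, not on the outcome. Here the two can coincide. A patient who converts may start a cholinesterase inhibitor or memantine because of the conversion. Under the rule as written, that patient then leaves the set on which the primary hazard ratio is estimated.

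The word used in the rule makes this harder to dismiss. The Background says these classes are not indicated in MCI, and Study design says they are not indicated during follow-up. In the article's own usage, conversion is the point at which they become indicated. A programmer who flags every participant with a record of either class would carry out the rule faithfully and delete events.

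Two things are at stake. The first is power, because a time-to-event comparison draws its information from events. The second is bias. The trial is single-blind, with only the neuropsychological assessor blinded, so prescribing after conversion could differ between the arms. If it did, the share of events removed would differ too.

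**Working it through.** **1. Reproduce the plan's sample size.** Inputs from Sample size and statistical analysis: hazard ratio 0.5 ("we cautiously set 50% reduction in the rate of conversion as estimated effect"), power 80–90%, overall conversion probability 12%, allocation 1:1. The significance level is not stated there; two-sided 0.05 is assumed.

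Schoenfeld: events d = (z for alpha/2 + z for power)² / (0.25 × (ln HR)²), and N = d / 0.12. With ln 0.5 = −0.6931, the denominator of d is 0.25 × 0.4805 = 0.1201.

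- 80% power: d = (1.960 + 0.842)² / 0.1201 = 65.3; N = 65.3 / 0.12 = 544.5. Stated: 544.
- 90% power: d = (1.960 + 1.282)² / 0.1201 = 87.5; N = 87.5 / 0.12 = 729.0. Stated: 728.

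The plan's figures reproduce. The Freedman formula (592 and 792) and a one-sided 0.05 level (429 and 594) do not. The sample-size arithmetic is not in question. It shows that the primary analysis needs 0.12 × 544 = 65.3 to 0.12 × 728 = 87.4 conversion events.

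**2. Power if the literal rule removes converters.** Power = Φ(√(0.25 × d) × 0.6931 − 1.960), where d is the number of events left. The share removed is an assumption, taken as equal in the two arms; the article gives no figure for it. The hazard ratio is held at 0.5.

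| Share of converters removed (assumed) | Events left, N = 544 | Power | Events left, N = 728 | Power |
|---|---|---|---|---|
| 0% | 65.3 | 80% | 87.4 | 90% |
| 25% | 49.0 | 68% | 65.5 | 80% |
| 50% | 32.6 | 51% | 43.7 | 63% |
| 75% | 16.3 | 29% | 21.8 | 37% |
| 100% | 0 | not estimable | 0 | not estimable |

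Example, 50% at N = 544: √(0.25 × 32.64) × 0.6931 − 1.960 = 0.020, and Φ(0.020) = 0.508.

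**3. Bias if the loss differs by arm.** Take no true effect and a 12% risk in each arm, and remove 50% of training converters but 25% of control converters (both shares assumed). Removed patients leave numerator and denominator.

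- Training: 0.12 × 0.50 / (1 − 0.12 × 0.50) = 0.06 / 0.94 = 0.0638.
- Control: 0.12 × 0.75 / (1 − 0.12 × 0.25) = 0.09 / 0.97 = 0.0928.
- Apparent hazard ratio: ln(1 − 0.0638) / ln(1 − 0.0928) = 0.68.

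With the shares reversed it is 1.48. Equal loss does little to the estimate: with a true hazard ratio of 0.5 and 50% removed in each arm, the apparent value is about 0.49.

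**The case against.** The strongest reply is that the sentence describes protocol deviations and was never meant to reach converters. Several places support this.

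- The Table 2 footnote makes AD diagnosis the patient's endpoint, so the primary observation is complete before any drug is started because of it.
- Study design presents drug therapy on conversion as planned care, not as a deviation.
- Table 1 lists cholinesterase inhibitors and NMDA antagonists as forbidden medication, and removing users of forbidden medication is a usual per-protocol criterion.
- The same sentence pairs the drug criterion with failure to keep up training. Endpoint criteria ends training at AD diagnosis, so an equally literal reading of that half could also catch converters, which suggests that the whole sentence concerns the period before the endpoint.
- The trial is sized on 12% of patients converting, so the authors expect conversions to be counted.

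This stands as evidence of intent. It does not supply the missing limit, because none of these places qualifies the exclusion rule.

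Three further replies stand in part. Study design does not name the drug started at conversion; the link to the two classes comes from the sentence before it and from the Background. A converter given neither class stays in the set, so the loss may be well below 100%. The ITT analysis keeps every converter, but it is not the primary analysis. Finally, a fuller protocol or analysis plan may carry the timing limit. That is possible, but the point here is a rule that the article states without limit and that conflicts with its other sections, not a detail it leaves out.

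A reader might go further and infer that the trial plans to discard its endpoint events. The documents do not support that as a statement of what will happen; it follows from one literal reading only. A reader might also conclude that patients given these drugs before diagnosis must stay in the primary set. That would override a criterion the authors chose on purpose, in order to estimate the effect of training strictly. It is a separate trade-off and is not needed to remove this contradiction.

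**Conclusion.** The concern holds as a defect in how the primary analysis set is defined. The exclusion is not limited to use before AD diagnosis, and read together with Study design, Outcome measures and Background it allows the endpoint to trigger removal from the primary analysis.

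The size is conditional. Under the intended reading that seems likely, this mechanism removes no converter and power is unaffected. Under the literal reading, losing half the converters brings power down by 27 to 29 percentage points, and losing all of them leaves nothing to estimate. Those figures rest on assumed shares, a two-sided 0.05 level and the plan's own hazard ratio of 0.5. The article does not show how many converters would receive either class, and no particular share should be read into it. The apparent hazard ratios of 0.68 and 1.48 under no effect likewise illustrate what unequal loss could do; they do not predict it.

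**What to change.** Reconcile Study design, Outcome measures and the per-protocol definition in Sample size and statistical analysis by stating three things:

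1. The drug exclusion applies only to cholinesterase inhibitor or memantine use before AD diagnosis.
2. Use that starts at or after the diagnosis is never a reason for exclusion.
3. A patient otherwise in the per-protocol set who is diagnosed with AD counts as an event at the diagnosis date.

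The cost is a sentence or two in the analysis-set definition. To apply the rule, the start date of any such drug is compared with the diagnosis date. No extra visits or patients are needed, the sample size stays as it is, and nothing about patient care changes.

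### Read where it stands, the off-trial rule for patients who cannot operate the device can remove training-arm patients only, after allocation, and the article does not say whether they stay in follow-up and in the ITT set

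*Protocol article*

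**What the plan says.** Four parts of the protocol article bear on this.

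- **Sample size and statistical analysis.** After describing 1:1 allocation and the sealed codes, the text says "The odd number means the training group, while the even number means the control group". The next sentence is the rule: "If the patient cannot be trained because of difficulty in operating computer or cellphone, the patient will be managed as off-trial". No time point is given and off-trial is not defined. The same section states that "we used per-protocol set instead of intention-to-treat (ITT) analysis as primary endpoint analysis". It removes from the per-protocol set patients who do not keep up the training, and adds an ITT analysis as a second approach.
- **Recruitment, screening and run-in period.** In the run-in, "they will receive blood tests, electrocardiogram, cranial MRI and a basic computer operation test". Afterwards, "Then all the eligible patients will be registered before baseline assessment". The consequence of failing the computer test is not stated.
- **Baseline assessment and randomization.** "After the baseline assessment, patients will be randomly allocated into two groups", so the computer test comes before allocation for every patient.
- **Intervention and follow-up.** The trained arm is described thus: "All the participants in the intervention group will login an online training website with their own passwords by either cell phone or tablet computer", whereas "participants in the control group will be required to neither alter their daily lifestyle nor receive any additional cognitive training".

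Device ability is not named in the inclusion, exclusion or withdrawal criteria.

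**The concern.** A patient can be found unable to train only if asked to train, and only the training arm is asked. A control with the same difficulty stays in. If the rule operates after allocation, the arms are no longer comparable as randomised.

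The likely direction is in favour of training. In MCI, trouble with a phone or tablet plausibly goes with worse cognition, older age or less schooling. Age and education are the trial's own stratification factors. Difficulty that first appears during three years of training could also be an early sign of the decline that the primary outcome counts.

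A filter that treats both arms alike is already in the design: the run-in computer test. The rule is not tied to it. What is at stake is chiefly the ITT analysis, which is the planned check on a per-protocol primary analysis.

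**Working it through.** **1. Order of events.** Run-in computer test (everyone), registration, baseline assessment, randomisation, odd/even arm assignment, then the off-trial sentence. From this order and from the condition that the patient cannot be trained, the natural reading is that the rule acts after allocation and in one arm.

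**2. Which analysis is affected.**
- Per-protocol (primary): patients who do not keep up training are already excluded. Those who cannot operate the device would probably leave this set under that rule, so the off-trial sentence adds little.
- ITT: unaffected if off-trial patients are still followed and counted; affected if they are not. The article does not say which.

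**3. The plan's own figure.** Inputs: hazard ratio 0.5, power 80–90%, overall conversion probability 12%. No alpha is stated; 0.05 two-sided is assumed because it reproduces the result.

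Events = (1.96 + z_power)² / (0.25 × (ln 0.5)²)

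- 80%: 65.35 events; 65.35 / 0.12 = 544.5 (plan: 544)
- 90%: 87.48 events; 87.48 / 0.12 = 729.0 (plan: 728)
- With 10% dropout: 544 / 0.9 = 605 and 728 / 0.9 = 809 (plan: approximately 600–800)

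The figures reproduce, and this point does not depend on them.

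**4. Illustration of the bias in an analysis that loses these patients.** Let x be the share of the training arm removed and r their hazard relative to the rest. Neither is in the documents; both are assumptions. With no true effect:

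Apparent HR = 1 / [1 + x(r − 1)]

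For n patients per arm and three-year risk p: control events = n·p; training events = n(1 − x)[1 − (1 − p)^HR]; d is their sum; a = (1 − x)/(2 − x).

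One-sided false benefit = Φ( −ln(HR) × √(d·a(1 − a)) − 1.96 )

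The values of n are 300 and 400 per arm less 10% dropout, that is 270 and 360.

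Worked case: x = 10%, r = 2, n = 270, p = 12%. HR = 1/1.10 = 0.909. Control events 32.4; training events 243 × (1 − 0.88^0.909) = 26.7; d = 59.1; a = 243/513 = 0.474. The shift is 0.0953 × √(59.1 × 0.249) = 0.366, and Φ(−1.594) = 5.5%.

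| Removed (x) | Relative hazard (r) | Apparent HR | False benefit, p = 12%, n = 270 | p = 12%, n = 360 | p = 16.5%, n = 360 |
|---|---|---|---|---|---|
| 1% | 1.5 | 0.995 | 2.6% | 2.6% | 2.7% |
| 1% | 2 | 0.990 | 2.7% | 2.8% | 2.8% |
| 2% | 2 | 0.980 | 3.0% | 3.1% | 3.2% |
| 5% | 1.5 | 0.976 | 3.1% | 3.2% | 3.4% |
| 10% | 2 | 0.909 | 5.5% | 6.2% | about 7% |

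The nominal value is 2.5%. The last column uses 1 − exp(−0.06 × 3) = 16.5%, from the 6.0 per 100 person-years that the plan cites and rounds to 17% over three years. It is shown because the plan's 12% is an overall probability, and with no effect the risk could be nearer the cited rate. Solving the two-group mixture exactly at 12% gives HR 0.976 (5%, r = 1.5) and 0.913 (10%, r = 2), so the simple formula is adequate.

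**The case against.** A reader might infer that every analysis is biased, ITT included, because off-trial patients are no longer followed. The article does not say that. Off-trial is undefined, and device difficulty is not named among the withdrawal criteria. An ITT analysis is planned precisely to deal with crossover and dropout. The ITT claim is therefore conditional.

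A reader might also take the timing as settled. It is inferred from the position and wording of the sentence. A pre-randomisation screen may have been meant, since everyone takes the computer test in the run-in.

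Entry is not wholly unguarded either. The inclusion criteria ask for expected good compliance with therapy, and the exclusion criteria have a catch-all for anything that prevents completion. The run-in is meant partly to judge compliance, and Table 2 rechecks eligibility at run-in and baseline. An investigator could turn away a patient who fails the test on these grounds. What slips through after a device test, in patients with MMSE 24–28, at least primary schooling and a caregiver, may be small, perhaps 1–2%.

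Finally, adding this loss to the per-protocol losses would risk counting the same patients twice.

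All of this stands, and it limits the size and certainty of the point. It does not remove it: the sentence as placed reaches one arm only, no criterion makes the test a condition of entry, and nothing states that these patients stay in the ITT set.

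**Conclusion.** The point holds as a should-fix. Read where it stands, the rule is a one-arm exclusion after randomisation, plausibly of higher-risk patients, with a bias towards training. Its own contribution falls on the ITT analysis, and only if off-trial ends follow-up or removes the patient from that set.

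The size cannot be derived from the documents. Under the assumed 1–10% removal at 1.5–2 times the hazard and no true effect, the apparent hazard ratio lies between 0.995 and 0.91. One-sided false benefit lies between about 2.6% and 6% at 12% risk, and reaches about 7% at 16–17% risk with 360 per arm. If only 1–2% are removed at twice the hazard, it is about 2.7–3.1%, close to nominal. The documents do not support a firm statement that all analyses are biased.

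**What to change.** - Add one eligibility line: passing the run-in computer operation test is required of all patients before randomisation.
- Replace the off-trial sentence with a statement that any randomised patient later unable to train stays in the assigned arm, in follow-up and in the ITT set. This concerns follow-up and analysis, not how the patient is managed.
- Reconcile the new wording with the withdrawal criteria and with the run-in section.
- For any patient already taken off-trial, obtain AD status at month 36 where consent allows, and include it in the ITT analysis.

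The cost is one added line, one replaced sentence and a few more screen failures. The test is already performed, and the 544–728 calculation does not change.
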